## Abstract

**Background:**

The proximal humerus fracture is a common injury, but the optimal management is much debated. The decision for operative or nonoperative treatment is strongly influenced by patient specific factors, regional and cultural differences and the preference of the patient and treating surgeon. The aim of this study is to compare operative and nonoperative treatment of proximal humerus fractures for those patients for whom there is disagreement about optimal management.

**Methods and analysis:**

This protocol describes an international multicenter prospective cohort study, in which all patients of 18 years and older presenting within three weeks after injury with a radiographically diagnosed displaced proximal humerus fracture can be included. Based on patient characteristics and radiographic images several clinical experts advise on the preferred treatment option. In case of disagreement among the experts, the patient can be included in the study. The actual treatment that will be delivered is at the discretion of the treating physician. The primary outcome is the QuickDash score at 12 months. Propensity score matching will be used to control for potential confounding of the relation between treatment modality and QuickDash scores.

**Discussion:**

The LADON study is an international multicenter prospective cohort study with a relatively new methodological study design. This study is a “natural experiment” meaning patients receive standard local treatment and surgeons perform standard local procedures, therefore high participation rates of patients and surgeons are expected. Patients are only included after expert panel evaluation, when there is proven disagreement between experts, which makes this a unique study design. Through this inclusion process, we create two comparable groups whom received different treatments and where expert disagree about the already initiated treatment. Since we are zooming in on this particular patient group, confounding will be largely mitigated. Internationally the treatment of proximal humerus fractures are still much debated and differs much per country and hospital. This observational study with a natural experiment design will create insight into which treatment modality is to be preferred for patients in whom there is disagreement about the optimal treatment strategy.

**Trial registration:**

Registered in Netherlands trial register NL9357 and Swiss trial register CH 2020–00961; https://clinicaltrials.gov/.

## Introduction

The proximal humerus fracture is a common injury, accounting for 5.7% of all fractures and the third most common fracture type in the elderly population [1,2]. The optimal management of acute proximal humerus fractures, i.e. operative or nonoperative treatment, is much debated [3–5]. Several meta-analyses have been inconclusive whether operative treatment of proximal humerus fractures is superior to nonoperative treatment [3–5].

The Proximal Fracture of the Humerus Evaluation by Randomization (PROFHER) study, a multicenter randomized controlled trial including 250 patients, is to date the largest study that compared outcomes following operative and nonoperative treatment of proximal humerus fractures. The PROFHER trial evaluated the Oxford Shoulder Score, the Short-Form 12, complications, subsequent therapies, and mortality. The study found no statistically significant or clinically relevant differences in outcomes between the operative and nonoperative treatment groups [6]. However, the validity and generalizability of these findings have been called into question [7,8]. The inclusion of patients in the PROFHER trial was not consecutive. In total, 1250 patients were screened, of which 563 patients were found eligible for inclusion. However, only 250 patients eventually consented to take part in the study. Furthermore, the 109 patients who received operative treatment were treated by 66 different surgeons in 30 different hospitals. The low number of cases per surgeon could have influenced the results of this study. What is more, since the inclusion rate is so low, generalizing results from such a selective group is not straightforward [9].

In practice, patient-specific factors can have a large impact on the decision for operative or nonoperative management, which leads to challenges during surgical trials. Furthermore, both patients and surgeons can have a strong preference for a certain treatment, which forms an obstacle for randomization in surgical trials [10]. The patient populations encountered in daily clinical practice often differ from the highly selected patient populations enrolled in randomized controlled trials [11].

In contrast, observational studies tend to have much larger sample sizes than randomized trials and thus provide an opportunity to investigate a variety of patient populations [12,13]. Observational studies could complement results of randomized trials, provided incomparability of patients who receive different treatment modalities (i.e., confounding) is adequately controlled for. A natural experiment, based on e.g. practice variation, could be considered, for example when recommendations for operative or nonoperative management are largely influenced by training of the treating surgeons [14]. For instance, a natural experiment could be set up by comparing two countries with a different preference for operative or nonoperative treatment of proximal humerus fractures, such as Switzerland and the Netherlands, respectively [15,16]. The aim of this multicenter international prospective cohort study is to compare outcome after management of proximal humerus fractures between Switzerland and the Netherlands by evaluating outcomes of patient populations in daily clinical practice, where disagreement exists about operative or nonoperative treatment.

## Methods and analysis

The LADON study will be an international multicenter prospective cohort study with the following participating centers from the Netherlands (University Medical Centre Utrecht (UMCU), Diakonessenhuis (DIAK), Sint Antonius Ziekenhuis (SAZ), where the predominant preference is for nonoperative treatment and from Switzerland (Cantonal Hospital of Lucerne (LUKS) and Kantonsspital Graubünden (KSGR)) with a predominant preference for operative treatment. This study protocol was written in adherence to the Standard Protocol Items: Recommendations for Interventional Trials (SPRIT) guideline [17].

### Participants selection

#### Inclusion criteria

All patients (>18 years) presenting with an acute displaced proximal humerus fracture involving minimally the surgical neck, including isolated greater tuberosity fractures are eligible for inclusion. Patient enrollment started the first of July 2020.

#### Exclusion criteria

Exclusion criteria include; open fracture, pre-existing co-morbidities which preclude operative treatment, pathological fractures, associated dislocation of injured shoulder joint, associated ipsilateral upper extremity fractures, concomitant soft tissue injury or neurovascular injuries requiring operative treatment, delayed presentation (> three weeks after injury), treatment for re-fractures, cognitive impairment, non-Dutch, non-German, or non-English speaking patients, patients not resident in the hospitals area and unavailable for follow-up.

### Intervention

The decision for operative or nonoperative treatment is left to the treating orthopedic trauma surgeon at the participating hospitals. The actual treatment will be initiated prior to inclusion in the LADON study.

#### Nonoperative treatment

Nonoperative treatment consists of sling immobilization for three to six weeks for comfort, adequate pain management and guided physiotherapy according to local protocol.

#### Operative treatment

The operative treatment consists of open reduction and internal plate fixation (ORIF), minimal invasive plate osteosynthesis (MIPO), intramedullary nailing, or arthroplasty of the glenohumeral joint. The decision for the type of operative treatment is left to the treating physician. Peri-operative management including anesthesia, antibiotics and thromboembolism prophylaxis will follow the national guidelines and local protocol.

### Expert panel progress

After informed consent, pseudonymized data sets including radiographs, AO fracture classification, and baseline patient characteristics during first presentation will be collected. The individual patient data sets will be made available on a secure online platform. All relevant data to reach a “clinical” decision will be made available, including basic clinical information, radiographs, key images of CT-scans if available and radiology reports. The data will be presented to an expert panel of each country, blinded to the already initiated treatment. The expert panels will consist of an equal distribution of representatives from both countries, three orthopedic trauma surgeons from the participating Dutch centers and three orthopedic trauma surgeons from participating Swiss centers. Members of each panel will independently decide on the preferred management, operative or nonoperative treatment, for each individual case. Patients can be included in the study if the majority of experts in one country, i.e., minimally two out of three, disagree with the received treatment in the other country. For example, patients are eligible if they would have received operative treatment based on the expert opinions in e.g. Switzerland, while in fact they received nonoperative treatment in the Netherlands, and vice versa. Patients will be excluded when the majority of the panel in one country agree on the received treatment in the other country. This will lead to a group of patients for whom there is disagreement on the optimal management, operative or nonoperative treatment. Both operative and nonoperative treated patients will be send to the expert panels to ensure blinding. A flow chart of the patient recruitment is shown in Fig 1. For practical efficiency we chose to perform the expert panel evaluation prior to inclusion rather than include all eligible patients and perform an expert panel evaluation afterwards.

**Fig 1 pone.0264477.g001:**
[figure not shown]
Flow chart of the patient recruitment.

In an ideal observational study all patient characteristics are measured and adjusted for. Instead of this utopia we try to identify patient subgroups for whom their profile is likely similar. We assume the patient profile is a continuum, such that on one end of the continuum all patients will receive conservative treatment, whereas on the other end of the continuum all patients will receive operative treatment. However, different hospitals (or countries) may have different preference for operative or conservative treatment, which provides a contrast that forms the basis for an observational study of these treatments. By zooming in on a patient with a similar profile, confounding by patient characteristics will, to a large extent, be mitigated. One way of identifying patients with a similar profile is to identify those patients for whom experts disagree about the appropriate treatment. The more we zoom in, the better we adjust for confounding, however, the less precise estimates will be due to fewer patients being included in the study (Fig 2).

**Fig 2 pone.0264477.g002:**
[figure not shown]
Patient profile continuum and confounding. Patient profile is a continuum, on the one end all patients receive nonoperative treatment and on the other end all patients receive operative treatment, this can differ per country. By zooming in on patients with a similar profile, confounding will be mitigated to a large extent.

### Outcome measures

#### Primary objectives

Primary outcome is assessed using the QuickDash score at 12 months following treatment. The QuickDASH is a patient-reported outcome instrument developed to measure upper extremity disability and symptoms, resulting in a score ranging from no disability (0) to most severe disability (100) [18].

#### Secondary objectives

Secondary functional outcomes include the QuickDash score at six weeks, the Subjective shoulder value (SSV), EuroQol five dimensional questionnaire (EQ-5D), Numerical Rating Scale (NRS) Pain score, return to sporting activity and return to work activity at 6 weeks and 12 months. The SSV is a subjective value for shoulder function expressed as a percentage of an un injured shoulder, which would score 100% [19]. The EQ-5D is a standardized questionnaire for generic health status measurements to asses quality of life [20].

Other secondary outcomes will include complications, revision surgery, implant removal and related complications. Complications will include cases of non-union, mal-union, superficial infection and fracture related infection, implant failure, confirmed deep venous thrombosis, myocardial infarction or stroke. Non-unions is defined as a minimum of six months with persistent pain and no signs of fracture healing on radiographic images. Mal-union defined as fracture union in an incorrect anatomical position on a radiograph or CT scan resulting in pain. Superficial infection is defined as redness, swelling, and/or purulent discharge from the wound that could be treated with oral antibiotics or wound incision. Fracture related infection is defined according to Metsemakers et al [21]. Implant failure is defined as loss of reduction, implant dislocation, implant breakage or breakage of screws. Revision surgery is defined as the need for secondary surgical treatment other than implant removal.

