### Data collection and patients follow-up

All patients will be reviewed at the standard six weeks and 12 months outpatient clinic visits after treatment. Standardized patient-reported outcome questionnaires will be collected during the outpatient visit, by performing telephone interviews or using a secure online questionnaire platform: Castor Electronic Data Capture (EDC) system. Electronic medical records will be reviewed to collect baseline characteristics regarding history of previous injuries of the affected shoulder, age, sex, BMI, ASA sore, trauma date, trauma mechanism, time from injury to treatment, current profession, and physical demands. Data collection will be performed by reviewing electronic medical records, operative reports, radiology reports and patient interviews by independent research fellows. All data will be stored in a research folder that can only be accessed by the principal investigator and independent research fellows. Data will be pseudonymized and a file to decode these data will be stored in a research folder only accessible by the principal investigator and independent research fellows.

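### The complication list names deep venous thrombosis but not pulmonary embolism, new nerve or vascular injury, or avascular necrosis, so the plan does not ensure that these are counted, or counted alike, in both groups

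*Protocol article*

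**What the plan says.** The protocol article sets the harm outcomes under Secondary objectives: "Other secondary outcomes will include complications, revision surgery, implant removal and related complications". It then itemises the first of these: "Complications will include cases of non-union, mal-union, superficial infection and fracture related infection, implant failure, confirmed deep venous thrombosis, myocardial infarction or stroke". Definitions follow for non-union, mal-union, superficial infection, fracture related infection (by citation) and implant failure. Reoperation has its own definition: "Revision surgery is defined as the need for secondary surgical treatment other than implant removal".

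Three other places bear on the list:

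- Operative treatment mentions thromboembolism as a peri-operative matter: "Peri-operative management including anesthesia, antibiotics and thromboembolism prophylaxis will follow the national guidelines and local protocol".
- Exclusion criteria contain the only mention of nerve or vessel injury, as a condition at entry: "concomitant soft tissue injury or neurovascular injuries requiring operative treatment".
- Data collection and patients follow-up gives the sources: "Data collection will be performed by reviewing electronic medical records, operative reports, radiology reports and patient interviews by independent research fellows".

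Trial status reports 102 patients included in the Netherlands, all treated conservatively so far, and 80 in Switzerland, all treated operatively so far.

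**The concern.** The list is uneven on its own terms. It counts one form of venous thromboembolism, together with myocardial infarction and stroke, but not pulmonary embolism. It has no item for a nerve or vascular injury that appears after treatment, although the operative group comprises plating, nailing and arthroplasty. Avascular necrosis is also absent. That nerve injury and avascular necrosis are recognised harms here is clinical background; the article does not say so.

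The study is meant to show which treatment is preferable where experts disagree. Complications, revision surgery and implant removal are the only harm outcomes that the article names. If some events are left out, or picked up differently in the two groups, the harm side of that comparison is incomplete or distorted.

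**Working it through.** **The plan's own figure.** The article gives no complication rate, so there is none to reproduce. Its group size rests on QuickDASH alone: 2 × (1.960 + 0.842)² × 14² / 8² = 48.1, so 49 per group (49.05 by the t-test, hence 50). This agrees with the stated 2 x 50. Complications do not enter it.

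**Where each event appears in the article.**

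| Event | Named as an outcome? | Mentioned elsewhere? |
|---|---|---|
| Deep venous thrombosis | Yes, if confirmed | Within thromboembolism prophylaxis (Operative treatment) |
| Pulmonary embolism | No | Only as part of thromboembolism prophylaxis, not by name |
| New nerve or vascular injury | No | Only injury at entry (Exclusion criteria) |
| Avascular necrosis | No | No |

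There is no general item for other complications. The phrase on related complications stands after implant removal and is undefined. Revision surgery captures an unlisted event only if it leads to another operation.

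**If the list is closed.** Unlisted events are not counted as complications. The expected number of patients affected in a group is n × p.

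- n: after the plan's own losses, 220 × 0.8 × 0.6 = 105.6, about 53 per group. Statistical analysis places only the primary analysis in the matched set, so n could be as high as 220 / 2 = 110 if the groups are equal.
- p: the proportion with at least one unlisted event. The article gives none. The range of 5% to 15% is purely an assumption.
- With n = 53: 53 × 0.05 = 2.7 to 53 × 0.15 = 8.0 patients.
- With n = 110: 110 × 0.05 = 5.5 to 110 × 0.15 = 16.5 patients.

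These are upper bounds for patients wrongly shown as free of complications, because some would also have a listed event or a revision.

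**If the list is open.** Recording of unlisted events then depends on whoever documents and extracts them. Let the true proportion p be the same in both groups, and let r be the share of such events recorded in each country. The apparent treatment difference is

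p × (r in Switzerland − r in the Netherlands).

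It is zero if recording is alike. It can be no larger than p, which is 5 to 15 percentage points under the assumed range. Its sign is unknown, because the article gives neither r.

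**Can the analysis remove it?** The propensity model contains age, sex, BMI, ASA score and AO classification. None of these describes recording practice. Adjusting for country is not possible either: among the 102 + 80 = 182 patients so far, country and treatment coincide completely.

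**The case against.** The strongest objection is that the article says complications 'will include' the listed events, not that they are limited to them. Fellows review medical records, operative reports, radiology reports and interviews, and the full protocol and case report form are not shown. A reader might infer from the list that the three events are reported in neither group, or that a patient with pulmonary embolism is scored as free of complications. The text contains no such rule, and that inference is not supported. The objection does not settle the matter, however. The article chooses to itemise and define this outcome, and an open list without common definitions leaves unlisted events to local practice in a study where locality and treatment coincide.

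A reader might also infer that the omissions flatter surgery. This is not shown. Implant failure and wound infection are already listed, implant removal is a separate outcome, and all of these arise essentially after surgery. The entry criterion on neurovascular injury concerns the state at entry and says nothing about harm from treatment.

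Finally, lasting disability from a nerve injury or avascular necrosis could still show in the 12-month QuickDASH, shoulder value or pain score. That is true, but it would not appear as a complication.

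**Conclusion.** The point holds as a gap in a secondary outcome. The list counts confirmed deep venous thrombosis, myocardial infarction and stroke but not pulmonary embolism, new nerve or vascular injury, or avascular necrosis, and it has no catch-all. The plan therefore does not ensure that these events are counted, or counted alike, in both groups. The complete overlap of country and treatment so far means that a difference in recording could not be told apart from a difference in harm.

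No size can be taken from the article. The counts and percentage points in the working rest on an assumed rate of 5% to 15% and only illustrate scale. The net direction of bias is not established. The primary outcome, its analysis and the sample size are unaffected. The change is worth making because it is cheap and concerns the study's harm comparison.

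**What to change.** In Secondary objectives:

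- Replace 'confirmed deep venous thrombosis' with 'confirmed venous thromboembolism (deep venous thrombosis or pulmonary embolism)'.
- Add 'nerve or vascular injury not documented before start of treatment'.
- Add 'avascular necrosis of the humeral head on available radiograph or CT'.
- State that the definitions apply identically to both groups.

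Extract these items from the sources already named under Data collection and patients follow-up, and re-extract them for patients already enrolled. The change concerns outcome recording only and alters no treatment.

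The cost is protocol and analysis plan wording and a few extra fields in the existing record review, with no new visit or imaging. There are two limits to report. Avascular necrosis can be seen only in patients who were imaged, so give the number imaged per group. Treatment starts before inclusion and the listed baseline data contain no neurological status, so show nerve deficits whose pre-treatment status is undocumented separately rather than counting them as new.

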### Statistical analysis

Descriptive results will be presented as mean values with standard deviations and range (SD, range), median values with interquartile range (IQR) or absolute numbers and percentages (%). To control for potential confounding, we will conduct propensity score matching. The propensity score will be estimated using binary logistic regression analysis, with operative or nonoperative treatment as the dependent variable and age, sex, BMI, ASA score, AO classification as covariates in the model. The primary analysis will be performed within the dataset of propensity score matched patients. Normal distribution will be confirmed using the Shapiro–Wilk test. Correlation between continuous variables will be measured using the Pearson correlation coefficient. Missing data will not be imputed. Differences between study groups will be analysed using the independent sample t-test, Mann–Whitney U test, or the Chi-square test. A two-tailed p-value less than 0.05 will be considered significant.

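### Revision surgery does not clearly count a first operation after failed nonoperative treatment, and loss of reduction counts only as implant failure, so early nonoperative failure may go uncounted

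*Protocol article*

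**What the plan says.** The protocol article, under Secondary objectives, names the safety and reoperation outcomes: "Other secondary outcomes will include complications, revision surgery, implant removal and related complications". It then lists the complications: "Complications will include cases of non-union, mal-union, superficial infection and fracture related infection, implant failure, confirmed deep venous thrombosis, myocardial infarction or stroke".

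Four definitions matter here:

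- Revision surgery: "Revision surgery is defined as the need for secondary surgical treatment other than implant removal".
- Implant failure: "Implant failure is defined as loss of reduction, implant dislocation, implant breakage or breakage of screws".
- Non-union: "Non-unions is defined as a minimum of six months with persistent pain and no signs of fracture healing on radiographic images".
- Mal-union: "Mal-union defined as fracture union in an incorrect anatomical position on a radiograph or CT scan resulting in pain".

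The section Nonoperative treatment says: "Nonoperative treatment consists of sling immobilization for three to six weeks for comfort, adequate pain management and guided physiotherapy according to local protocol". It does not mention later conversion to surgery, and no outcome of that name is listed. Under Data collection and patients follow-up, records, operative reports and radiology reports are reviewed, with no restriction to one group. Under Statistical analysis: "Differences between study groups will be analysed using the independent sample t-test, Mann–Whitney U test, or the Chi-square test", with significance at a two-tailed p below 0.05.

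**The concern.** The two treatments can fail in the same way: the fragments move and the patient needs an operation. For the groups to be compared fairly on later surgery, that event has to be recorded under the same rule in both. The definitions follow the course of an operated patient, and the nonoperative counterpart has to be fitted in by interpretation.

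Two things are at stake. First, the Discussion says the study will inform which treatment should be preferred. The need for later surgery is a natural counterweight to the functional score, so an undercount on one side matters to that judgement. Second, the ambiguity works in one direction, because the narrower reading can only lower the nonoperative count. Under Trial status, all 102 Dutch inclusions so far are nonoperative and all 80 Swiss inclusions are operative. If sites interpret the definition differently, the difference in coding cannot be separated from the difference in treatment.

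**Working it through.** **Step 1. Apply the definitions to the same events in each group.**

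| Event | Initially operated | Initially nonoperative |
|---|---|---|
| Early loss of reduction | Complication (implant failure) | No listed item at that time |
| Operation for it, e.g. at four weeks | Revision surgery | Narrow reading: not counted. Broad reading: revision surgery |
| Non-union (at least six months) | Complication | Complication |
| Painful mal-union | Complication | Complication |
| Implant removal for a complication | Implant removal, not revision | Same, but only after conversion |

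The first two rows treat the groups differently. Non-union and mal-union do not fill the gap for early failure. The first needs six months and the second needs the fracture to have united, so a patient who displaces and is operated on at four weeks meets neither at that time.

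**Step 2. Which reading does the text support?** The phrase about secondary surgical treatment can mean a second operation (narrow) or surgery after the initial treatment (broad). The label revision and the exception for implant removal both presuppose an earlier operation, so the narrow reading is the more natural one. The text does not settle it.

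**Step 3. Size of the shift.** The documents give no revision or conversion rate, so there is no stated figure to reproduce. Let r be the revision rate in operated patients and c the share of nonoperative patients who later have surgery.

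- Broad reading: risk difference (operative minus nonoperative) = r − c.
- Narrow reading, if no converted patient has a further operation: r − 0 = r.
- Shift = r − (r − c) = c, against surgery. It is somewhat smaller if some converted patients are operated on again and so are counted.

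With r assumed at 10%:

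| c (assumed) | Broad | Narrow |
|---|---|---|
| 0% | +10 points | +10 points |
| 5% | +5 | +10 |
| 10% | 0 | +10 |
| 15% | −5 | +10 |

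**Step 4. Could this produce a significant result?** Take 50 per group (Sample size considerations) and r = c = 10%, so the true difference is zero and the narrow reading compares 10% with 0%. By the normal approximation:

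- pooled rate 0.05; standard error under the null √(0.05 × 0.95 × 2/50) = 0.0436
- standard error under the alternative √(0.10 × 0.90/50) = 0.0424
- (0.10 − 1.96 × 0.0436)/0.0424 = 0.34, a probability of about 63%.

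The approximation is rough with counts this small. Against 0/50, the uncorrected chi-square test needs at least 4 events and Fisher's exact test at least 6. For a binomial(50, 0.10) count these have probabilities of 75% and 38%.

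As single tables: the planned 220 patients leave 220 × 0.8 × 0.6 = 105.6 after the stated losses, about 53 per group. Then 6/53 (11%) against 0/53 gives p = 0.012 (chi-square) or 0.027 (Fisher). With 110 per group, 6/110 (5.5%) against 0/110 gives 0.013 or 0.029.

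**The case against.** The strongest reply is that the definition of revision surgery nowhere requires an earlier operation. On its literal wording, a plate or arthroplasty after a failed sling can be secondary surgical treatment. A reader might infer that only operated patients can have this outcome, but the document does not say so. This objection stands, and it makes the point one of unclear definition and not of proven bias.

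A reader might also infer that failed nonoperative care is counted nowhere, or that the nonoperative count is necessarily zero. Neither is supported. Non-union and painful mal-union count in both groups, the complication list is introduced in open terms, and operative reports are reviewed for everyone. A converted patient kept in the initial group has an implant and can afterwards have implant failure, infection or a further operation. What remains is the early failure in Step 1.

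Leaving implant removal out of revision surgery is not evidence of bias against surgery. It lowers the operative revision count, which works the other way, and removal is reported as its own outcome. That implant failure needs an implant is likewise inherent. The fair point is only that loss of reduction sits under that heading without a nonoperative counterpart.

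The Statistical analysis section gives a general list of tests and names no reoperation hypothesis. The illustration uses chosen rates: at 53 per group, six events is the smallest count for which Fisher's test falls below 0.05 (5/53 against 0/53 gives about 0.057). Both limits stand.

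Finally, this is a condensed article and event coding may be fuller elsewhere. But the article does print the definitions, and the difficulty lies in what they say.

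**Conclusion.** The point holds as a weakness in how secondary outcomes are defined. It is unclear whether a first operation after failed nonoperative treatment is counted, and loss of reduction is tied to an implant. Early nonoperative failure may therefore go uncounted while the same event in an operated patient is both a complication and a revision.

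On the narrow reading, the comparison of later surgery shifts against surgery by the conversion rate, provided converted patients have no further counted operation. The conversion rate is not given, so the size is unknown. The 10% figures and the p-values show only that a moderate rate could produce a significant difference where none exists. On the broad reading the shift in later surgery disappears, though loss of reduction is still counted unequally.

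The primary QuickDASH comparison is not affected. The change is worth making because it is cheap and the possible error runs in one direction.

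**What to change.** - Make the between-group outcome any unplanned operation on the injured shoulder after the initial treatment, up to 12 months. It should count conversion from nonoperative treatment, re-operation, and implant removal done for a complication.
- Keep every patient in the initial treatment group for this outcome.
- Count loss of reduction or secondary displacement in both groups, as an item separate from implant failure.
- Report implant-specific events and elective implant removal descriptively, without a between-group test.

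This removes the ambiguity whichever reading was intended. It needs no new visits or patients, because records and operative reports are already reviewed in both groups. The cost is a wording change and a recode of data already collected. The small downside is that each implant removal must be classified as elective or done for a complication.
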